## Unscheduled visits

If the participant is unwell, they will be strongly encouraged to seek treatment with the study team and given emergency contact numbers to facilitate this. Out of hours’ participants will be advised to contact the study clinician and in the event of an emergency, to attend Kilifi County Hospital. Subjects will be required to be resident in KHDSS during the study. Medical emergency plans will be in place with the possibility to admit patients to the Aga Khan Hospital in Mombasa, should intensive care be required. Transport related to unscheduled (and scheduled) visits will be reimbursed.

## End of treatment visit

The final visit for each cohort will be at 6 months. As per
Table 3 and
Figure 2, this will include adverse event recording. If adverse events have occurred, the final visit may be later, at the discretion of the study team. If adverse events are ongoing, follow-up will be continued until the event resolves or until the condition has stabilised.

## Follow-up visit(s)

Each subject will participate in a single treatment period only, and they will be in an in-patient facility starting from the day before dosing until 24 hours after last dose. The multi-dosing regimen is for a period of up to 72 hours and participants will therefore be monitored for 72 to 96 hours. Out-patient visits at KEMRI-CGMRC or the in-patient facility will be arranged on day 2, 5 and day 42 post-dose for the single dosing group. The multiple dosing group will be reviewed as an out-patient on day 5 and day 42. All participants will undergo telephone follow-up at 6 months. Depending on emerging data, additional visits (including additional telephone consultations) may be required.

## Study restrictions

### Dose escalation holding criteria

If any of the following scenarios occur within a group with reasonable possibility of a causal relationship with unithiol, dose escalation will be stopped pending safety review, prior to higher dose levels being evaluated. In the case a serious adverse event occurring, this will be reported in accordance with section 11.7 of this protocol, including reporting to the Sponsor and the DSMB within 48 hours.

Clinically relevant signs or symptoms or intolerable adverse events of similar nature occur in 2 or more subjects in a group that in the opinion of the Investigator warrant stopping of dose escalationOne or more subjects report a serious adverse event considered by the Investigator to be related to the study drugTwo or more severe adverse events occur which are considered by the Investigator to be related to the study drugDose escalations will only occur after a minimum period of days, depending on the dose received (as specified in
Figure 1a and
Figure 1b).

### Cohort dosing holding criteria

If any of the following scenarios occur within a group with reasonable possibility of a causal relationship with unithiol, further dosing within a cohort will be stopped pending review by the Data Safety Monitoring Committee.

Clinically relevant signs or symptoms or intolerable adverse events of similar nature occur in 2 or more subjects in a group that in the opinion of the Investigator warrant stopping of dose escalationOne or more subjects report a serious adverse event considered by the Investigator to be related to the study drug
*
Two or more severe adverse events occur which are considered by the Investigator to be related to the study drug

* If a serious adverse event were to occur during sentinel dosing, then dosing of other subjects would be held until review by the DSMB.

Should the threshold for a holding rule be met, there would be a study hold then an
*ad-hoc* DSMB meeting would be convened before further dosing. All safety follow-ups would continue as planned.

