## Dose escalation schedule

In every cohort, subjects will be dosed at least 30 minutes apart. In cohorts C2, C3 and C4, 1 participant will receive a sentinel dose prior to the remaining 7 participants being dosed. Minimum time-periods of observation between dose escalations are summarised in
Figure 1a and
Figure 1b.

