**Figure 1b. f1b:**
[figure not shown]
Multiple dosing escalation strategy. DSMB, Data and Safety Monitoring Board; IV, intravenous administration; PO, oral administration. Days represent the minimum period between dose escalations. Longer intervals may be required. Time interval until DSMB meetings represent the earliest possible meeting and later meetings may occur.

C2 begins with a sentinel dose and the remaining 7 subjects will be dosed at least 24 hours after this. C3 will begin with a sentinel dose and the remaining 7 subjects will be dosed 72 hours after this. Cohort C4 will be dosed a minimum of 1 week after C3 and will also commence with a sentinel dose followed by 3 days until the remaining 7 subjects are dosed. The CIV cohort will be dosed in tandem with C3. Dose escalation decisions will not be dependent on the results of the pharmacodynamic assay, as this analysis is exploratory and has not been validated. Between the single dosing stage and the multiple dosing stage, preliminary pharmacokinetic data will be made available
*.* Multiple dosing will only proceed once the DSMB have reviewed adequate pharmacokinetic data from the single dosing stage to be satisfied that the proposed dosing regimen will not lead to accumulation of the study drug. A minimum of one week after the final dose is given in CM1, dosing of CM2 will commence. The flowchart (
Figure 1) summarises the process of dose escalation.

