Serious Adverse Event (SAE)	A serious adverse event is any untoward medical occurrence that: • results in death • is life-threatening • requires inpatient hospitalisation or prolongation of existing hospitalisation • results in persistent or significant disability/incapacity • consists of a congenital anomaly or birth defect Other ‘important medical events’ may also be considered serious if they jeopardise the participant or require an intervention to prevent one of the above consequences. NOTE: The term "life-threatening" in the definition of "serious" refers to an event in which the participant was at risk of death at the time of the event; it does not refer to an event which hypothetically might have caused death if it were more severe. “Hospitalisation” signifies that the subject has been detained (usually involving an overnight stay) at a hospital for observation and/or treatment above that routinely offered at the inpatient trial facility. When in doubt as to whether hospitalisation occurred or was necessary, the adverse event will be considered as serious. Hospitalisation for elective surgery or routine clinical procedures, which are not the result of an adverse event, will not be considered adverse events and should be recorded on a clinical assessment form and added to the CRF.
Serious Adverse Reaction (SAR)	An adverse event that is both serious and, in the opinion of the reporting Investigator, believed with reasonable probability to be due to one of the trial treatments, based on the information provided.
Suspected Unexpected Serious Adverse Reaction (SUSAR)	An adverse reaction, the nature or severity of which is not anticipated based on the applicable product information is considered as an unexpected adverse drug reaction. Where the adverse reaction is also considered to have a possible, probable, or definite relationship with the drugs given, and also meets the criteria for a serious adverse reaction, it is termed a Suspected Unexpected Serious Adverse Reaction (SUSAR). These events are subject to expedited reporting as for SAEs.

To avoid confusion or misunderstanding of the difference between the terms ‘serious’ and ‘severe,’ the following note of clarification is provided: ‘severe’ is often used to describe intensity of a specific event, which may be of relatively minor medical significance. ‘Seriousness’ is the regulatory definition supplied above. Detailed guidance can be found here:

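### One related grade 3 event that is clearly non-serious in the lone sentinel of C2, C3 or C4 triggers no mandatory hold in the visible text

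*Protocol article*

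**What the plan says.** The Dose escalation schedule states: "In cohorts C2, C3 and C4, 1 participant will receive a sentinel dose", with seven participants to follow. The text below Figure 1b gives the waiting times:

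- C2: "C2 begins with a sentinel dose and the remaining 7 subjects will be dosed at least 24 hours after this"
- C3: "C3 will begin with a sentinel dose and the remaining 7 subjects will be dosed 72 hours after this"
- C4 "will also commence with a sentinel dose followed by 3 days until the remaining 7 subjects are dosed"

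The Cohort dosing holding criteria list three triggers for stopping further dosing within a cohort, all subject to a reasonable possibility that unithiol is the cause:

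1. Similar clinically relevant or intolerable events in at least two subjects, if the investigator thinks they warrant stopping.
2. At least one related serious adverse event.
3. "Two or more severe adverse events occur which are considered by the Investigator to be related to the study drug"

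A footnote adds the only rule for the sentinel stage: "If a serious adverse event were to occur during sentinel dosing, then dosing of other subjects would be held" until the DSMB has reviewed the case.

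Table 7 equates severe with grade 3, for which hospitalisation is possible but not required. Table 5 and the note beneath it keep severe and serious apart. Table 5 counts hospitalisation as detention at a hospital for "observation and/or treatment above that routinely offered at the inpatient trial facility" and resolves doubt towards seriousness: "When in doubt as to whether hospitalisation occurred or was necessary, the adverse event will be considered as serious".

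**The concern.** The interval after a sentinel exists so that a bad reaction in one person is seen and acted on before seven more are exposed. The thresholds for severe events, however, are counted over a cohort of eight and then applied at a stage when only one person has been dosed. With one subject, a rule that needs two subjects cannot be met, and a rule that needs two severe events is met only if the same person has both. The footnote shows that the authors wanted a separate rule for the sentinel, but it names serious events only.

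This matters because the article's Conclusions say that the safety and tolerability of oral doses above 300 mg are not yet confirmed. C2 goes from 300 mg to 900 mg, and the Ethics section names sentinel dosing as one of the extra precautions at higher doses. For one category of event, that precaution rests on judgement alone.

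**Working it through.** The plan states no operating figure for the holding rule, so there is none to reproduce. The check has a logical part and an arithmetic part.

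**Which rules fire when only the sentinel has been dosed (events judged related)**

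| Sentinel outcome | Criterion 1 (≥2 subjects) | Criterion 2 or footnote (serious) | Criterion 3 (≥2 severe) | Mandatory hold |
|---|---|---|---|---|
| One grade 3, non-serious | no | no | no | **no** |
| One grade 3, serious | no | yes | no | yes |
| Two grade 3, non-serious | no | no | yes | yes |

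The gap is the first row only.

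**Is that row a real category?** The default for doubtful hospitalisation narrows it but does not empty it. Care that the trial unit routinely offers is not hospitalisation under Table 5. Table 8 grades a temperature above 39.0°C or a pulse above 130 as severe, and either may be managed in the unit and remain non-serious.

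**Does another visible rule close it?**
- The Dose escalation holding criteria use the same three thresholds.
- The Data and safety monitoring board section ties planned meetings to dose escalation and the summary of severe events to the review of serious ones.
- Safety analyses ties adverse event reports to dose escalation.
- The clause that lets investigators or the local safety monitor refer events to the DSMB is worded for events that are neither serious nor severe.
- The text below Figure 1b sets waiting times, with no review attached.

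**Does criterion 3 protect the seven once they start?** Subjects may be dosed 30 minutes apart, so six gaps × 0.5 h = 3 h covers all seven. Table 1 gives a Tmax of 3.7 h after 300 mg orally. If Tmax is similar at higher doses (an assumption), all seven could be dosed before the first reaches peak concentration. A second severe event may then come too late to spare the others.

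**Size.** Subjects behind sentinels: 3 × 7 = 21. Let *p* be the per-subject rate of such an event. The documents give none, so 2%, 5% and 10% are assumed, with independence between subjects and the same rate in each cohort.

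- Another event among the seven, given one in the sentinel: 1 − (1 − p)^7
- Sentinel event and at least one more, per cohort: J = p × [1 − (1 − p)^7]
- The same, in at least one of three cohorts: 1 − (1 − J)^3
- At least one hold if one event were enough: 1 − (1 − p)^3
- Expected holds if one event were enough: 3p

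| p | Another among 7 | J | Three cohorts | At least one hold | Expected holds |
|---|---|---|---|---|---|
| 0.02 | 0.13 | 0.0026 | 0.0079 | 0.059 | 0.06 |
| 0.05 | 0.30 | 0.0151 | 0.0446 | 0.143 | 0.15 |
| 0.10 | 0.52 | 0.0522 | 0.1485 | 0.271 | 0.30 |

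Under the current text, the chance of a mandatory hold after one such sentinel event is zero at every *p*. With the amended rule it is one.

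**The case against.** **Unseen material.** A review step after the sentinel could sit in Figure 1a, the DSMB charter or the full version 2 protocol. This stands as a limit: the point concerns the visible text only. Still, the article does not leave the rule elsewhere. It sets out numbered thresholds and their consequence, and those thresholds have the gap.

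**Discretion.** Table 5 lets important medical events be classed as serious, which would bring the footnote into play. The DSMB may meet ad hoc and receives summaries of all adverse events. The C2 wait is a minimum. The referral clause was probably meant to extend the route to lesser events, not to bar worse ones. All of this is fair, and a careful investigator would probably pause. None of it requires a pause.

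**Deliberate choice.** The two-event threshold appears in both sets of criteria. The note on severity says that severe events can be of minor medical importance, and a malarial fever could reach grade 3. This is a reason to expect some unnecessary holds. It does not explain why the same count should apply when only one person has been dosed.

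**Assumed rates too high.** The article cites 216 workers given 1,000 mg intramuscularly with no adverse events reported. The one-sided 95% upper bound is 1 − 0.05^(1/216) ≈ 1.4%. At the quoted 39% oral bioavailability, 1,500 mg delivers about 0.39 × 1,500 = 585 mg. At p = 1.4%, J is about 0.13% and the three-cohort figure about 0.4%. This is a reasonable argument for the low end of the range, and nothing in the documents supports 10%. However, how well that report captured adverse events is unknown, and intramuscular absorption would have to be near complete for the comparison to hold.

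**Conclusion.** The point holds for the visible text. One related, clearly non-serious grade 3 event in the sentinel of C2, C3 or C4 meets no holding criterion, so the protocol can be followed exactly while seven more volunteers are dosed without review. The gap is narrow: it closes if the event is serious or if the same sentinel has a second related severe event.

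The absolute chance of harm from the gap is small at low rates, about 0.8% over three cohorts at an assumed 2%, and rises to 15% at an assumed 10%. These figures rest on assumed rates, independence and a common rate across cohorts. Confidence is medium, because the escalation figures and the charter are unseen. The amendment is worth making as an inexpensive safeguard; the gap is not a major flaw in the design.

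**What to change.** Extend the footnote to the Cohort dosing holding criteria. For example: *One serious adverse event, or one severe (grade 3) adverse event that the investigator considers related to the study drug, in a sentinel participant holds dosing of the remaining seven until DSMB review.* Put the same rule in the DSMB charter. If the charter already has it, bring the protocol into line.

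The text change is one line, but it needs a formal amendment through the sponsor, the ethics committees and the regulator, and screening is already under way. The operating cost is an occasional ad hoc DSMB meeting and a short delay. At the assumed 2%, 5% and 10%, the chance of at least one such hold over the three cohorts is about 6%, 14% and 27%, or 0.06, 0.15 and 0.30 expected meetings. Some further holds will follow events that later prove unrelated, because the category of possible relationship in Table 6 needs only one of its conditions and a fever above 39.0°C counts as severe.

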### Concomitant medication

This will be assessed at the time of the first screening visit and the participants will be asked if they have taken any medication within the past 3 months. Medications taken within 3 months of the screening study will not necessarily result in exclusion, rather this will be at the discretion of the principal investigator (PI). The study team will emphasize to participants the importance of the medical team overseeing clinical care during the study period. Participants will be encouraged to contact the study team for all medical attention during the study. If any medication is required, the name, strength, frequency of dosing and reason for use will be documented in the participants source data. Participants will be asked to phone the study team should they require medical review or change in contraception.

Appropriate contraceptive medication is an acceptable concomitant medication and is an inclusion criterion for women of childbearing age (as per section 6.1.2 Screening). Should a participant require a prescription for contraception they would be referred to KCH services or their local health Centre/dispensary.

## Patient obligations

### Diet

Standard meals will be provided for all subjects whilst they are resident at the trial unit. Dietary requirements will be confirmed at the screening visit. Dietary intake is unlikely to affect elimination of unithiol as the drug is renally excreted and is not subject to metabolism by liver enzymes.

During periods of intensive pharmacokinetic blood sampling (the day of dosing), meals will be identical for each group. Otherwise, meals will not be restricted.

### Alcohol

Subjects will adhere to the following alcohol restrictions:

Alcohol is not permitted from 36 hours before check-in until discharge from the inpatient facility. Participants will be made aware of this. There will not be active efforts to police this restriction.Alcohol is not permitted 36 hours prior to non-residential visits.Alcohol intake is unlikely to have a significant effect on the assessment of safety or pharmacodynamic or pharmacodynamic during this trial. There may be a modest (diuresis induced) increase in renal excretion of unithiol following alcohol intake.

### Smoking

No restrictions. Standard health and safety procedures (such as not smoking in the health facility) will be in place.

### Exercise

No restrictions.

### Blood donation

Subjects must not donate blood from enrolment until 3 months after the final follow-up visit.

### Contraception

Use of an effective method of contraception for the duration of study (and until 2 months after last receiving the study drug) for female participants aged 18–64 years (unless permanently sterile following hysterectomy). For those not on effective contraception, referral to an appropriate family planning service will be offered. For female participants, we will ask them to attend with their family planning records for verification. Effective contraception is defined as a contraceptive method with failure rate of less than 1% per year when used consistently and correctly, in accordance with the product label. Examples of these include combined oral contraceptives, injectable progestogen, implants of etenogestrel or levonorgestrel, intrauterine device or intrauterine system, male condom combined with a vaginal spermicide (foam, gel, film, cream, or suppository), and male condom combined with a female diaphragm, either with or without a vaginal spermicide (foam, gel, film, cream, or suppository).

### Prior/concomitant therapy

The study team will emphasize to participants the importance of the medical team overseeing clinical care during the study period. Participants will be encouraged to contact the study team for all medical attention during the study. If any medication is required, the name, strength, frequency of dosing and reason for use will be documented in the participants source data. Participants will be asked to phone the study team should they require medical review or change in contraception.

### Prohibited medication

Participants will be encouraged to seek medical care from the study team during their follow-up period. Participants will be discouraged from taking over the counter medications and medications from other providers except in urgent situations, where delay to treatment could be harmful. Receipt of a concomitant medication for an acute illness would normally not lead to exclusion from the trial.

## Participant withdrawals

### Subject withdrawal criteria

Subjects will be withdrawn for multiple reasons including some of those listed below:

Any clinically relevant signs, symptoms, or adverse events that in the opinion of the Investigator warrant subject withdrawalNon-compliance with the study restrictions, as considered applicable by the InvestigatorLoss to follow up (applies to a subject who consistently does not return for protocol study visits, is not reachable by telephone or any other means of communication and/ is not able to be located).At the discretion of the Investigator, if inter-current illnesses occur that may invalidate the study data, if the subject was enrolled in violation of the study protocol, or if a significant protocol violation occurs (note, asymptomatic malaria infection is not anticipated to require exclusion from the study, although subjects will be monitored closely)Subject decisionOn the advice of DSMB

### Managing withdrawals

If a subject is withdrawn, the reason will be recorded in the case report form (CRF). If withdrawal is the result of a serious adverse event (AE), the investigator will offer to arrange for appropriate specialist management of the problem and the ethical committee, DSMB and regulatory authority will be informed in a timely manner. The extent of follow up will be determined by a medically qualified investigator but will be at least for the whole study period. Subjects withdrawn prematurely for any reason will not receive further doses of unithiol, although they will be encouraged to come back to the clinic for safety evaluation. Additionally, participants will not receive the IMP if they do not meet the eligibility criteria.If a participant withdraws from the study, blood samples collected before his/her withdrawal from the trial will be used/stored unless the participant specifically requests otherwise. In all cases of subject withdrawal, apart from those of complete consent withdrawal, long-term safety data collection for participants, including some procedures such as safety blood investigations, will continue so far as the participant is willing to consent. Where participants withdraw consent for follow up, this will be respected and follow up will be discontinued. If a volunteer withdraws/is withdrawn from the study after receiving unithiol, they will be encouraged to continue to complete the recommended period of safety monitoring. If the subject requests to leave after taking unithiol but before being discharged from the inpatient facility, they will be offered telephone follow-up.

